### Significance levels of tests and confidence intervals

All statistical tests will use a two-sided *p* value of 0.05, unless otherwise specified. There will be no formal adjustment of *p* values for any interim analyses performed. Two-sided 95% confidence intervals will be presented for all estimates.

### Baseline comparability

Baseline characteristics will be summarised by randomised treatment arm. Categorical variables will be summarised by number and percentage in each category; continuous variables will be summarised by mean and standard deviation, or median and interquartile range, as appropriate. No statistical tests of differences in baseline characteristics between groups will be done, as any differences between treatment arms must be due to chance rather than bias.

### Adjustment for design factors

Since randomisation is stratified by surgeon and presence of OA in two adjacent joints (subtalar and talonavicular), analyses of outcomes will involve adjustment for these factors (as recommended in ICH E9, section 5.7 [20]) unless otherwise indicated. Treatment effects will then be estimated conditional on surgeon and presence of OA in the two adjacent joints.

Baseline MOXFQ walking/standing domain will also be adjusted for in primary analyses where this is the outcome. Similar adjustment will be made for all continuous secondary outcome variables where a baseline measurement is recorded.

### Follow-up and losses to follow up: missing data

Missing baseline covariate data are not anticipated since covariates must be recorded to allocate treatment.

We expect that up to 10% of patients will not provide measurements at 52 weeks post-op. Numbers and percentages of missing data at each visit (baseline, weeks 26 and weeks 52) will be tabulated by treatment group for the primary and secondary outcomes (Additional file 1: Table S2).

All observed data will be included in the primary and secondary analyses. Missing outcome data will be assumed to be missing-at-random (MAR) conditional on the observed values of all other variables included in the analysis models, and so independent of the values of the unobserved data itself. As the primary outcome is the change from baseline, patients without baseline and at least one outcome score will consequently not be included in the analysis. Their inclusion, however, would not add any information to the analysis [21].

The characteristics of patients missing 52-weeks MOXFQ data will be evaluated and a sensitivity analysis will be done to examine the impact of departures from the MAR assumption (described below).

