### Randomisation and blinding

The randomisation process was based on a minimisation algorithm. The algorithm gave an overall 85% chance of allocating the patient to the treatment arm which was under-represented with respect to three stratifying variables: surgeon, presence of OA in subtalar joint, and presence of OA in talonavicular joint (as determined by pre-operative MRI scan [7]). The research nurse or delegated individual logged on to the sealed envelope randomisation service and provided patient information (including on stratifying variables) and the surgical treatment to be received was supplied immediately.

Patients were allocated in a 1:1 ratio to the TAR and arthrodesis arms. It was not possible to blind patients, surgeons, radiologists, and clinical assessors for the following reasons: surgeons know what procedure they are performing, radiologists and patients will be able to identify from radiographs which procedure has taken place, and patients who receive ankle arthrodesis and their assessors will invariably know their ankle is stiff (a known consequence of arthrodesis surgery) whereas those undergoing TAR will retain motion in the ankle. To protect against allocation bias, the person recruiting the patient to the study was not aware of the allocation to be assigned prior to contacting the randomisation service.

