## Outcomes

### Primary outcome measure

The primary outcome measure is the absolute difference between the two treatment arms in self-reported pain-free function, as measured by the Manchester-Oxford Foot Questionnaire (MOXFQ) walking/standing domain score [8] at 52 weeks post-op. The 52-week score will be used if it was taken in a window from 48 to 56 weeks post-op.

The MOXFQ standing/walking domain score has been found to be a valid and responsive measure to evaluate all types of foot and ankle surgery [9, 10], and it has additionally been shown to be more responsive for the outcomes of foot and ankle surgery patients than generic QoL measures such as the EuroQol five-dimension quality-of-life instrument (EQ-5D) and the Short Form (36) Health Survey (SF-36) [11].

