### Calculation of outcome scores

#### The Manchester-Oxford Foot Questionnaire (MOXFQ)

Responses to each MOXFQ questionnaire item consist of a five-point Likert scale ranging from no limitation (scoring 0) to maximum limitation (scoring 4). Items are grouped into three domains: walking/standing (seven items), pain (five items), and social interaction (four items). Domain scores are computed by summing the patient’s responses to each item within the domain and converting to a 0–100 metric, where higher scores represent greater severity.

If a single item within any domain is unanswered it will be imputed with the mean of the respondent’s answers to the other items within that domain. If two or more questions on any domain are unanswered the overall score for that domain will not be calculated and its value will be set to missing [12]. If the entire questionnaire has not been completed all MOXFQ domain scores for that visit will be set to missing.

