## Sample size

The sample size calculation for the primary outcome (change in MOXFQ walking/standing domain by 52 weeks post-op) was performed using Stata/IC version 12.1 [15]. It was based on achieving 90% power to detect the minimal clinically important difference (MCID) in the primary outcome at the 5% level of significance, accounting for expected loss to follow-up. The trial is multi-centre and the outcome plausibly varies by surgeon, so the sample size was adjusted to account for clustering; the intraclass correlation coefficient (ICC) was estimated based on previous studies, and the initially computed sample size was inflated by a factor f = 1 + (m − 1) ∗ ICC [16].

The sample size calculation was partly based on the study by Dawson et al. [9] which defined the MCID in the MOXFQ when evaluating outcomes following surgery for hallux valgus. They defined it as the mean change in MOXFQ of those patients who reported feeling at least “slightly better”, and found it to be 16, 12, and 24, respectively, for the standing/walking, pain, and social interaction domains of the MOXFQ. For this trial we determined it was important to detect a difference of 12 in the change from baseline in MOXFQ standing/walking domain between the two treatment arms; a conservative choice given the threshold for a MCID in the standing/walking domain found in the Dawson et al. study was 16. The standard deviation of the walking/standing domain of the MOXFQ was estimated as 27 [11], and loss to follow-up was estimated as 10% (attrition in similar RCTs has been 5–7% [17]).

Based on these quantities, the required sample size was estimated as 118 patients per arm. Assuming an average cluster size (m) of 14 (patients per surgeon) and an ICC of 0.03 (estimated from the median of ten previous surgical studies reporting patient-reported disease-specific measures 12 months post-surgery [18]), an inflation factor of f = 1.39 was estimated, leading to a final required sample size of 164 per arm or 328 patients total.

The assumptions of ICC = 0.03 and equal numbers of patients per surgeon in the sample size calculation [19] were reviewed by the trial statistician prior to the end of recruitment using the available data. The review indicated lower ICC and also some variability in numbers of patients per surgeon compared to the original assumptions (ICC < 0.01; average cluster size = 15, standard deviation = 9.6), resulting in increased power.

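### A patient with a follow-up MOXFQ score but no baseline score does carry information, so the stated reason for excluding such patients is wrong

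*SAP article*

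**What the plan says.** The section on follow-up and missing data makes four statements that bear on this point.

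- It promises completeness: "All observed data will be included in the primary and secondary analyses". The section on the patient population makes the same promise for observed outcome data under intention to treat.
- It then requires both a baseline and at least one follow-up score for a patient to be analysed. The reason given is that the primary outcome is a change from baseline.
- It says of the patients left out: "Their inclusion, however, would not add any information to the analysis".
- It expects no problem with covariates: "Missing baseline covariate data are not anticipated since covariates must be recorded to allocate treatment".

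Other sections bear on those statements. Randomisation and blinding lists what the minimisation used: "three stratifying variables: surgeon, presence of OA in subtalar joint, and presence of OA in talonavicular joint". The MOXFQ scoring section says: "If two or more questions on any domain are unanswered the overall score for that domain will not be calculated". The primary outcome measure and model (1) both take the follow-up score as the response, and baseline MOXFQ enters model (1) as a covariate. The sections on adjustment for design factors and on continuous secondary outcomes carry the same baseline adjustment over to the secondary scores.

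**The concern.** The exclusion rule covers two kinds of patient with a single justification. A patient with a baseline but no follow-up score contributes nothing to a likelihood for follow-up scores, so leaving that patient out costs nothing. A patient with a 26- or 52-week score but no baseline has an observed outcome under a randomised allocation, and that outcome informs the treatment difference.

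Both supporting reasons fail for this second kind of patient. The change-from-baseline premise does not match model (1), where the outcome exists without a baseline. The assurance about covariates holds for surgeon and the two OA indicators, but baseline MOXFQ is not among the allocation variables, and the scoring rule shows how a baseline domain score can become missing.

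At stake are a little precision and the consistency of the primary analysis set with the stated intention-to-treat principle. Because each continuous secondary model includes its own baseline, the same loss can occur there.

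**Working it through.** **The plan's own figure.** With a difference of 12, SD 27, two-sided 5% and 90% power, n per arm = 2 × (27 × (1.960 + 1.2816) / 12)² = 106.4, so 107. Allowing for 10% loss gives 107 × 1.1 = 117.7, rounded to 118 (106.4 / 0.9 = 118.2 agrees). The design effect is 1 + 13 × 0.03 = 1.39, and 118 × 1.39 = 164.0, hence 164 per arm and 328 in total. The stated figures reproduce and are not in dispute.

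**Inputs for the check**

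- From the article: 303 randomised, 10% expected loss (303 × 0.9 = 272.7 with a 52-week score), SD 27, difference 12, 1:1 allocation.
- Assumed, because the article does not give them: baseline-to-52-week correlation ρ of 0.3 to 0.7, and a share m of 1% to 10% of those 272.7 patients lacking a baseline (about 3 to 27 patients).
- Surgeon clustering and the 26-week score are ignored.

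**Information per patient.** Baseline adjustment reduces the outcome variance from σ² to σ²(1 − ρ²). An outcome-only patient therefore carries a fraction 1 − ρ² of a complete patient's information: 0.91, 0.75 and 0.51 at ρ = 0.3, 0.5 and 0.7. The plan treats this as zero.

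**Standard error with and without these patients**

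- Information, excluded: N(1 − m) / [4σ²(1 − ρ²)]
- Information, included: the same plus Nm / (4σ²)
- SE = 1 / √information

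For ρ = 0.3 and m = 5%:

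- Excluded: 259.1 / (4 × 729 × 0.91) = 0.0976, SE 3.20.
- Included: 0.0976 + 13.6 / (4 × 729) = 0.1023, SE 3.13.

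| ρ | SE excluded, m = 5% | SE included, m = 5% | Fall |
|---|---|---|---|
| 0.3 | 3.200 | 3.126 | 2.3% |
| 0.5 | 2.905 | 2.850 | 1.9% |
| 0.7 | 2.396 | 2.364 | 1.3% |

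Over the whole assumed range, information rises by 0.5% (ρ = 0.7, m = 1%) to 10% (ρ = 0.3, m = 10%). The largest power gain for 12 points is at ρ = 0.3 and m = 10%, from 95.4% to 96.9%, about 1.5 points.

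**Simulation.** 4,000 trials of 273 patients with a true difference of −12 compared complete-case ANCOVA with mean-imputed baseline. Baselines were missing completely at random.

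| ρ | Share missing | Empirical SE, complete case | Empirical SE, mean-imputed |
|---|---|---|---|
| 0.3 | 5% | 3.189 | 3.106 |
| 0.3 | 20% | 3.569 | 3.184 |
| 0.5 | 5% | 2.919 | 2.858 |
| 0.5 | 20% | 3.214 | 2.949 |
| 0.7 | 5% | 2.407 | 2.415 |
| 0.7 | 20% | 2.582 | 2.536 |

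All average estimates lay between −11.95 and −12.04, so neither method showed bias. At ρ = 0.7 simple mean imputation gives little or no gain, because it weights outcome-only patients as heavily as complete ones although their residual variance is larger.

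**The case against.** **The rule may be harmless as written.** The sentence is correct for patients with no follow-up score, who are probably the larger group given up to 10% expected loss. The exclusion could also be read as meaning patients who lack baseline and outcome alike. The stated reason, change from baseline, points to the other reading. Even on the kinder one, model (1) needs a baseline value for each patient, and the plan supplies none when it is missing. The source cited for the sentence is not available here, but no source could make it true of a patient with an observed outcome.

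**Missing baselines may hardly occur.** This stands as a limit on size. The plan to tabulate missing baseline data is routine reporting and does not show that any are expected. The two-item scoring rule applies at every visit and shows only that a baseline score can be missing.

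**A head count overstates the loss.** A reader might use √(n/(n − k)), which for 15 of 273 gives √(273/258) = 1.029, or 2.9%. That counts an outcome-only patient as a complete one and is therefore a ceiling.

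**The visit window.** A reader might infer that the plan also throws patients away through its window: "The 52-week score will be used if it was taken in a window from 48 to 56 weeks post-op". The documents do not support that. A prespecified window legitimately defines which observation is the 52-week score. The article does not state what happens to a score outside it; non-use is only implied. At most a score is lost, since a patient with a baseline and a 26-week score stays in the repeated measures model. The window does not alter analysis by randomised arm. The sentence about adding no information is not applied to it, and no figure shows that any score falls outside it.

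**Conclusion.** The point holds for patients with a follow-up score but no baseline score. For them the no-information statement is false, both supporting reasons fail, and the exclusion contradicts the promise to use all observed data.

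Its practical size is small. At an assumed 5% of baselines missing, the standard error falls by about 2% at most when these patients are kept, and power moves by no more than about 1.5 points even at an assumed 10%. These figures rest on assumed correlations of 0.3 to 0.7, an assumed rate of missing baselines, and no clustering. A reader might infer that the rule biases the comparison; nothing in the article or the check shows this. The case for change is a wrong statement and an internal contradiction in the definition of the primary analysis set, not a material loss of power.

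**What to change.** - Limit the no-information sentence to patients with no follow-up score, and drop the change-from-baseline reason for the exclusion.
- Limit the statement on covariates to the three allocation variables.
- Keep every patient with at least one follow-up score. Where only the baseline is missing, impute the overall baseline mean ignoring arm, or model baseline as a response with a mean common to both arms. The second option avoids the weighting problem seen at high correlation. Either relies on baseline missingness being unrelated to arm, as it should be when the questionnaire is completed before allocation is known; the plan should say so.
- Apply the same rule to each continuous secondary outcome with a baseline covariate.
- Optionally, keep the 48 to 56 week window for the primary analysis and add a sensitivity analysis that includes 52-week questionnaires returned outside it.

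The cost is a few sentences and a line or so of code for mean imputation, or a somewhat larger model if baseline becomes a response. If no baseline score proves to be missing, the results do not change under mean imputation.

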### Statistical analyses

All analysis will be carried out using Stata version 15 (or above). The results of the analyses will be reported following the principle of the ICH E3 guidelines on the Structure and Content of Clinical Study Reports [22] and CONSORT guidelines [23].

### Recruitment and follow-up patterns

The number of patients screened for eligibility will be presented. Reasons for non-admissions into the trial will be reported in a tabular form (listed in the dummy tables in Additional file 1: Table S1).

The period of data collection, including the date of the first patient’s first visit and date of the last patient’s last visit will be described. Recruitment will be presented by year and centre. The throughput of patients from those screened, those randomised, and those assessed at each visit and included in the analysis will be summarised in a CONSORT flowchart [23]. The average time between pre-op assessment and surgery in each treatment arm will be reported. The number of patients who withdraw and are unwilling to provide follow-up will be reported by treatment arm, as will the number of missing baseline, 26-week, and 52-week CRFs (Additional file 1: Table S2). Other lower limb surgeries occurring within 12 months post-op will be reported by treatment arm, with information on the type of surgery and side of the body operated on.

### Baseline characteristics

Baseline characteristics will be summarised in a table by treatment arm. The variables to be reported in the baseline tables are listed in the dummy tables (Additional file 1: Table S3).

### Trial treatment

The number of patients undergoing their randomised surgery will be reported by treatment group. Although it is made explicit that patients cannot change surgical treatment arm once it has been randomly allocated, the clinician remains free to give alternative treatment to that specified in the protocol if it is felt to be in the best interest of the patient. Any cross-overs or other treatment deviations, as well as the number of patients who did not undergo surgery of any kind, will be specified along with reasons, as detailed in the protocol deviation log.

### Analysis methods

#### Primary analysis

A multilevel repeated measures linear regression model will be used to estimate the difference between the treatment groups in MOXFQ walking/standing domain score at 52 and 26 weeks post-op. Baseline scores will be adjusted for, so the model will return identical treatment effect estimates as a model for change from baseline to 26 or 52 weeks with the same baseline adjustment [24].

This analysis model will use all available visit data (from 26 weeks and 52 weeks) to strengthen confidence in the MAR assumption and give greater power to detect differences at individual visits.

The model for the MOXFQ walking/standing domain will include fixed effects for time (two categories, 26 weeks/52 weeks), treatment (two categories, TAR/ankle arthrodesis), treatment by time interaction, baseline MOXFQ walking/standing domain (continuous), and presence of OA in each of the two adjacent joints as determined by a pre-operative MRI scan (OA1, two categories, present/absent subtalar joint; OA2, two categories, present/absent talonavicular joint). A random patient effect will be included to take account of clustering by patient. A random surgeon effect, and an additional random surgeon by treatment coefficient, will also be included in the model to take account of clustering by surgeon and variation in the treatment effect by surgeon. This will be modelled with an unstructured covariance structure. The model will be fitted using restricted maximum likelihood estimation (REML).

The model for y_ijk_, the MOXFQ walking/standing domain value at follow-up (either 26 or 52 weeks), where i indexes the visit time, j the individual, and k the surgeon, will hence be:
1$$ {\mathrm{y}}_{\mathrm{ijk}}={\beta}_{0\mathrm{jk}}+{\beta}_{1\mathrm{k}}\left({\mathrm{treatment}}_{\mathrm{jk}}\right)+{\beta}_2\left({\mathrm{time}}_{\mathrm{ijk}}\right)+{\beta}_3\left({\mathrm{time}}_{\mathrm{ijk}}\ast {\mathrm{treatment}}_{\mathrm{jk}}\right)+{\beta}_4\left(\mathrm{baseline}\ {\mathrm{MOXFQ}}_{\mathrm{jk}}\right)+{\beta}_5\left({\mathrm{OA}1}_{\mathrm{jk}}\right)+{\beta}_6\left({\mathrm{OA}2}_{\mathrm{jk}}\right) $$

Where,
$$ {\displaystyle \begin{array}{l}{\beta}_{0\mathrm{jk}}={\beta}_0+{\mathrm{v}}_{0\mathrm{k}}+{u}_{0\mathrm{jk}}+{\varepsilon}_{\mathrm{ijk}}\\ {}{\beta}_{1\mathrm{k}}={\beta}_1+{u}_{1\mathrm{k}}\end{array}} $$

And,
$$ {\displaystyle \begin{array}{l}{\mathrm{v}}_{0\mathrm{k}}\sim \mathrm{N}\left(0,{\sigma}_v^2\right)\\ {}{u}_{0\mathrm{jk}}\sim \mathrm{N}\left(0,{\sigma}_{u0}^2\right)\\ {}{\varepsilon}_{\mathrm{ijk}}\sim \mathrm{N}\left(0,{\sigma}^2\right)\\ {}{u}_{1\mathrm{k}}\sim \mathrm{N}\left(0,{\sigma}_{u1}^2\right)\end{array}} $$

And,
$$ {\mathrm{treatment}}_{\mathrm{jk}}=1\ \mathrm{if}\ \mathrm{treatment}\ \mathrm{is}\ \mathrm{TAR}\ \mathrm{and}\ 0\ \mathrm{if}\ \mathrm{treatment}\ \mathrm{is}\ \mathrm{ankle}\ \mathrm{arthrodesis}. $$

The primary outcome is the average difference between treatment groups at 52 weeks, estimated as *β*_1_ + *β*_3._

Heterogeneity of surgeon cluster sizes may lead to model convergence problems. Although randomisation is stratified by surgeon, if a large number of surgeons only see a very few patients there may be insufficient data to estimate the random surgeon by treatment coefficient. If the primary analysis model fails to converge, the model will be refitted after excluding the random surgeon by treatment coefficient.

The model makes assumptions about random effects distributions, correlation structure, and residuals, which will all need investigation. If any assumptions are poorly met then transformation of the change in MOXFQ walking domain score may be required.

#### Secondary analysis

##### Continuous secondary outcomes

The treatment group difference in 26-week MOXFQ walking/standing domain score will be obtained from the primary analysis model (1) as *β*_1._

Each of the following continuous secondary outcome measures will be analysed using a separate multilevel repeated measures linear regression model:
MOXFQ pain domain scoreMOXFQ social interaction domain scoreFAAM-ADLFAAM-Sport (for patients involved in sport)EQ-5D IndexEQ-5D VASROM dorsiflexionROM plantarflexion

Similar to the primary analysis model, each model will include fixed effects for treatment, time, treatment by time interaction, baseline value of the associated score, and presence of OA in each of the two adjacent joints as determined by a pre-operative MRI scan. A random patient effect, a random surgeon effect, and a random surgeon by treatment coefficient will also be included in each of the models. If convergence problems are experienced, the approach outlined for the primary outcome will be followed.

